## Abstract

**Background:**

The core symptoms of bulimia nervosa (BN) and binge eating disorder (BED) are recurrent episodes of binge eating. Despite negative psychological and physical consequences, BN/BED patients show uncontrollable approach tendencies towards food. This cognitive bias occurs at an early stage of information processing. Cognitive bias modification (CBM) directly targets such biases and has been shown to be effective in treating several mental disorders. In alcohol addiction, automatic action tendencies towards alcohol cues and relapse rates were successfully reduced by a specific form of CBM, termed approach bias modification. Based on these findings and data from a proof-of-concept study in people with high levels of food craving, CBM is considered a promising new treatment approach for BN/BED. Given the similarities between BN/BED and addictive disorders, the rationale for using approach bias modification appears to be particularly strong. The aim of the present study is to examine whether, compared to a sham training, computerised approach bias modification (10 sessions) can reduce binge-eating episodes in BN/BED patients from pre-treatment to follow-up. Additionally, we will investigate whether this CBM programme also reduces global eating disorder psychopathology, trait and cue-elicited food craving, food intake as well as approach and attentional bias towards visual food cues. Treatment acceptance will be determined by attrition rates and responses on a feedback form.

**Methods:**

This is a double-blind, randomised, placebo-controlled, parallel-group superiority trial with two parallel arms. A total of 54 BN/BED patients will be recruited. Approach bias towards food will be retrained by a computer task adopting an implicit learning paradigm. Patients in the control condition (sham) will conduct a similar task but will not be trained to avoid food cues. Methods against bias include public registration, randomisation by a central study office, standardisation of the treatments and blinding of assessors. Furthermore, the session number and duration will be equivalent in the two conditions.

**Discussion:**

This is the first registered randomised controlled trial of approach bias modification in a clinical BN/BED sample. Results from this study will provide an indication of the efficacy of approach bias modification training for BN/BED and the potential mechanisms of action underlying this treatment.

**Trial registration:**

DRKS00010231 (retrospectively registered on 24 March 2016; first version)

## Background

Bulimia nervosa (BN) and binge eating disorder (BED) are common and serious mental disorders with elevated all-cause mortality, comorbidity and high relapse rates [1–4]. They share repeated episodes of binge eating as key characteristics [5]. Several authors have highlighted the addiction-like features in BN and BED [6–9] such as uncontrollable approach tendencies towards binge food despite significant negative psychological and physical consequences.

According to dual-process models, two distinct systems of information processing contribute to the evaluation of food cues and the control of eating behaviour, i.e. an impulsive system that operates rapidly and automatically (i.e. mostly outside of conscious control), and a reflective system that operates slower and more deliberately [10, 11]. The impulsive system evaluates food cues primarily regarding their current emotional and motivational significance. In contrast, the reflective system involves higher-order processes of cognitive control, deliberate decisions and impulse regulation that take long-term consequences into account. It is thought that in addictive disorders, the impulsive system dominates to a large degree the initiation of addictive behaviour, whereas the reflective system lacks power to control this behaviour [11]. Supporting this assumption, bulimic eating disorders such as BN and BED are associated with strong, impulsive responses and poor cognitive control towards food cues, which is considered to contribute to a heightened susceptibility to sensitised cues that trigger action tendencies and lead to binge eating [12]. Hence, even though people with a bulimic eating disorder may be aware of the negative consequences of binge eating, they may still engage in it when food cues are processed in the impulsive system. This is reflected by findings that individuals with bulimic eating disorders show appetitive physical responses towards food cues despite rating them as anxiety-provoking and disgusting [13, 14]. A rapidly growing body of research shows that eating disorders and unhealthy eating behaviour are associated with cognitive biases that unfold their negative effects in the impulsive system during the automatic processing of food cues, particularly by increasing attention and approach tendencies towards food [14–21].

Traditional (talking) psychotherapy programmes may not be best suited to directly modulate such biases that occur at an early stage in information processing and that often operate outside of conscious control [11, 22, 23]. In an effort to create more suitable interventions, researchers have translated findings from basic research and developed cognitive bias modification (CBM) programmes that are considered to provide a way to more directly target such biases. Different CBM programmes have been shown to be effective in treating mental disorders such as depression [24], social phobia [25] and addictive disorders [26–29]. With regards to the latter, several studies have used an approach bias modification training in alcohol-dependent participants and found this to effectively reduce automatic action tendencies towards alcohol cues and relapse rates [27, 29, 30]. Several meta-analyses have demonstrated the efficacy of CBM across different mental disorders [31–35]. Consequently, CBM has also been suggested as a potential new treatment approach for eating disorders [22, 23]. Recently, it was shown that approach bias modification reduces approach bias towards food cues and actual food intake in female student populations [36, 37]. However, it is yet unknown whether such a training is equally effective in clinical samples of patients with BN/BED. In addition, the efficacy may also depend on the use of multiple sessions of training [38].

In a proof-of-concept study [39] we recently evaluated the efficacy of such an approach bias modification training in a sample of people with high levels of food craving and subthreshold bulimic symptoms. Both the targeted approach bias towards food cues and also attentional bias towards food, trait and cue-elicited food craving, as well as more general eating disorder symptoms, were significantly reduced during the training with medium to large effect sizes in this study. The initial approach bias towards visual food cues was not only reduced (as hypothesised) but actually turned into an avoidance bias. Furthermore, all participants completed the intervention and the majority of them perceived the training as effective in altering daily eating habits. Taken together, these highly promising findings suggested that retraining automatic action tendencies in people with bulimic symptoms by means of computerised CBM may be an effective, feasible and acceptable way of reducing cognitive biases, food craving and binge eating. Thus, a randomised controlled trial with BN and BED patients appeared to be the logical next step.

According to the emotional distress hypothesis of binge eating, cognitive biases constitute latent vulnerability factors that become evident when the individual is confronted with a stressor [40]. Consequently, CBM should be most effective in its impact on cognitive biases and subsequent eating behaviour upon exposure to stressful situations. In fact, it has been demonstrated that CBM attenuates the effects of stressors on symptoms of depression and anxiety [41, 42]. Furthermore, there is a common theoretical basis and strong empirical evidence that negative affect (in response to a stressor) is a key trigger of attentional bias towards food and of binge eating [43–46]. Therefore, we applied a vulnerability-stress model for our CBM programme by using stimuli that induce moderate levels of negative affect before cognitive bias training and assessment.

### Aims

The central aim of this randomised controlled pilot trial is to examine whether a specifically tailored, brief (10 sessions), computerised CBM training (approach bias modification versus sham) is able to reduce binge-eating episodes in BN and BED patients (primary efficacy endpoint). More precisely, from pre-treatment to 2-month follow-up, BN and BED patients who receive real CBM are expected to report a greater reduction in the number of objective binge-eating episodes during the previous 2 months than those who receive sham CBM.

Additionally, we will investigate whether this CBM programme reduces global eating disorder psychopathology from pretreatment to follow-up, and trait and cue-elicited food craving, food intake and approach and attentional bias towards visual food stimuli in BN and BED patients from pre- to post-treatment. Finally, we will assess treatment acceptance by attrition rates and by means of a specifically designed feedback form. Specifically, as compared to patients in the sham CBM condition, patients in the real CBM condition are expected to show (1) decreased global eating disorder psychopathology from pre-treatment to follow-up, (2) decreased approach and attentional bias towards food cues, (3) decreased state food craving after cue exposure, (4) decreased trait food craving as well as (5) reduced food intake in a bogus taste test from pre- to post-treatment. In an exploratory analysis we will examine the patients’ acceptance of this specific CBM intervention, taking dropout rates and scores on a feedback form into account (treatment acceptance).

## Methods

### Design

This is a superiority trial adopting a double-blind, randomised, placebo-controlled, parallel-group design comparing real and sham CBM. Participants with BN or BED will be randomly allocated to receive either 10 sessions (15 min each) of real CBM (treatment group) or sham CBM (control group) in a period of 4 weeks. Participants will be recruited from two different sites (Heidelberg, Germany and London, UK). Outcomes will be assessed at baseline, post-treatment and 2-month follow-up. The study protocol is outlined in the flow chart in Fig. 1, and Table 1 provides details of all assessments at the different timepoints.

**Fig. 1 Fig1:**
[figure not shown]
Participant flow chart

**Table 1 Tab1:** ABBA study schedule of enrolment, interventions and assessments

	Study period						
	Treatment (real CBM) group and control (sham CBM) group						Control group only (optional)
	Enrolment	Pre-allocation	Allocation	Treatment	Post- treatment		Treatment
Timepoint	0	Baseline assessment (t1)	0	Weeks 1 –4	Follow-up (t2)	2- month follow-up (t3)	Weeks 1–4
Enrolment:							
Eligibility screen	X						
Informed consent	X						
Allocation			X				
Interventions:							
Real CBM				10 x			10 x
Sham CBM				10 x			
Assessments:							
Weight	X						
Questionnaires		X			X		
Computer tasks		X			X		
Taste Test		X			X		
Clinical interview		X				X	

*CBM* cognitive bias modification

#### Participants and recruitment

Participants will be recruited from the outpatient units of the Department of General Internal Medicine and Psychosomatics at University Hospital Heidelberg, the South London and Maudsley NHS Foundation Trust’s Specialist Adult Eating Disorders Unit, and through websites, circular mails, advertising posters and advertisements in the local media.

### Inclusion criteria

Women and men will be eligible for participation if they are aged 18 years or above and meet the criteria of a *Diagnostic and Statistical Manual of Mental Disorders, version 5* (DSM-5) diagnosis of BN or BED [5].

### Exclusion criteria

Exclusion criteria are: (1) age under 18 years, (2) medical (e.g. electrolyte abnormalities) or psychiatric (e.g. acute suicidality) instability, (3) the need for immediate inpatient treatment, (4) lifetime diagnosis of substance dependence, psychosis, bipolar disorder, attention deficit hyperactivity disorder (ADHD) or borderline personality disorder, (5) psychotropic medication use other than selective serotonin reuptake inhibitors (patients have to be on a stable medication, i.e. at least 14 days of a SRRI during participation in the trial), (6) severe learning disability that affects patients’ ability to complete study assessments/treatment, and (7) the inability to speak fluent English/German (depending on study site), impacting on patients ability to complete study assessments/treatment.

### Sample size

Previous randomised controlled trials comparing real and sham versions of approach bias modification in clinical samples applied a repeated measures ANOVA design (group × time) to examine treatment-specific changes and have reported small-to-medium effect sizes (η_p_^2^ between 0.05 and 0.06) [27, 29, 30]. Using the smallest effect size that has previously been reported, a total sample size of 40 patients will have 80 % power to detect an effect of this size using a 2 × 2 repeated measures ANOVA with a 0.05 two-tailed significance level. The percentage of data lost owing to errors in the applied neuropsychological tasks was 7 % at the maximum in previous studies. Taking this and a potential dropout rate of 25 % into account, a minimum of 53 patients must be included. Thus, we will recruit 27 patients for each group (total *n* = 54).

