### Analyses

To determine quality, completeness and variability of the outcome measures, descriptive statistical analyses and graphical methods will be used. To evaluate treatment-specific changes over time in patients, a 2 × 2 repeated measures ANOVA, with group as between-subject factor and time as within-subject factor, will be applied. The size of the treatment effect on the outcome measure (EDE) will be the difference in outcome data between those in the two treatment conditions at follow-up. Additionally, multiple regression models will permit exploration of the relationship between changes in the cognitive measures and symptom improvement. No interim analyses are planned. A two-tailed significance level of *p* < .05 will be used throughout. Both completer and intent-to-treat analyses will be performed. Missing values will be replaced by using the Last Observation Carried Forward (LOCF) method for the intent-to-treat analysis. As this is a pilot trial resources do not stretch to setting up a Monitoring Committee. Analyses will be conducted by the principal investigators. As CBM is a safe procedure with no known side effects we do not expect any unexpected adverse reactions, serious or unexpected serious adverse reactions. We will report any adverse reactions and serious adverse events. It is intended that the results of the study will be reported and disseminated by the principal investigators at international conferences and in peer-reviewed scientific journals.

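### The stated 80 % power with 40 patients is wrong: for a group × time partial eta-squared of 0.05, the planned 2 × 2 repeated-measures ANOVA has about 29 % power

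*Protocol article*

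**What the plan says.** All statements are in the protocol article.

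- **Source of the effect size (Sample size).** The earlier sham-controlled trials "applied a repeated measures ANOVA design (group × time) to examine treatment-specific changes" and reported "small-to-medium effect sizes (η_p_^2^ between 0.05 and 0.06".
- **Value used and power claim (Sample size).** The lower end of that range, 0.05, is taken: "Using the smallest effect size that has previously been reported, a total sample size of 40 patients will have" 80 % power for it, in a 2 × 2 repeated-measures ANOVA "with a 0.05 two-tailed significance level". No pre-post correlation and no conversion of the effect size is given.
- **Recruitment target (Sample size).** The 40 are raised to 53 for task errors and dropout, then rounded to 27 per group, 54 in total.
- **Planned analysis (Analyses).** The same test: "a 2 × 2 repeated measures ANOVA, with group as between-subject factor and time as within-subject factor, will be applied".
- **Status of the trial (Aims).** "The central aim of this randomised controlled pilot trial is to examine whether" the training reduces binge eating, which is named as the primary efficacy endpoint. The Design section calls the study a superiority trial.

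**The concern.** The planning effect and the planned test are on the same scale: both concern the group × time term of a repeated-measures ANOVA. With two groups and two time points, the F statistic for that term is the square of the two-sample t statistic on change scores. Its partial eta-squared is computed against the within-subject error, so whatever correlation exists between baseline and follow-up is already in it. Power then follows from the effect size, the sample size and alpha alone, with no further correlation to assume. A partial eta-squared of 0.05 is modest, and 40 patients looked far too few to detect it with 80 % power.

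At stake is how the primary result will be read. If the training works as well as in the cited trials, the primary test would miss it about seven times in ten, while the article tells readers to expect two in ten. A non-significant result would then look like evidence against the training when it says little either way.

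**Working it through.** **Inputs.** Partial eta-squared 0.05 (0.06 as the upper end), N = 40, two-tailed alpha 0.05 and a 2 × 2 repeated-measures ANOVA (Sample size, Analyses); 1:1 allocation (Randomisation). The interaction F has 1 and N − 2 = 38 degrees of freedom.

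**Step 1: convert the effect.** f² = 0.05 / (1 − 0.05) = 0.0526, so f = 0.229. In standard deviations of change, d = 2f = 0.46.

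**Step 2: reproduce the stated figure.** A common formula for this interaction takes f on the raw-score scale: λ = f² · N · m / (1 − ρ), with m = 2 measurements. The article gives no ρ; 0.5 is assumed here because it returns the stated number.

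- N = 40: λ = 0.0526 × 40 × 2 / 0.5 = 8.42, power 80.7 %.
- N = 38: λ = 8.00, power 78.6 %.

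So 40 is the smallest even total that reaches 80 %, which matches the article. Under this formula the answer depends on ρ. Power at N = 40 is 52 % for ρ = 0, 64 % for 0.25, 81 % for 0.5, 95 % for 0.7 and 99 % for 0.8.

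**Step 3: power for the effect the article names.** A partial eta-squared from the group × time test needs no factor m / (1 − ρ), so λ = f² · N.

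| Partial eta-squared | Patients analysed | λ | Power |
|---|---|---|---|
| 0.05 | 40 | 2.11 | 29.3 % |
| 0.05 | 54 | 2.84 | 38.0 % |
| 0.05 | 152 | 8.00 | 80.2 % |
| 0.06 | 40 | 2.55 | 34.4 % |
| 0.06 | 54 | 3.45 | 44.5 % |
| 0.06 | 126 | 8.04 | 80.3 % |

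Using λ = f² · (N − 2) changes little: 28.1 % at N = 40 and 36.9 % at N = 54 for 0.05. A simulation with 200,000 runs gave 29.2 % at N = 40. Even one-sided testing at N = 40 gives only 41 %.

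**Step 4: a check that needs no correlation.** The critical value of F(1, 38) is 4.10. An observed partial eta-squared of 0.05 with 40 patients gives F = 38 × 0.05 / 0.95 = 2.00, p = 0.165. Significance needs at least 4.10 / (4.10 + 38) = 0.097. If the planning effect, observed exactly, is clearly non-significant, power for it cannot be 80 %.

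**Step 5: the effect actually powered.**

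- N = 40: 80 % power needs λ = 8.27, so f² = 8.27 / 40 = 0.207, partial eta-squared = 0.207 / 1.207 = 0.17, d = 0.91.
- N = 54: λ = 8.15, f² = 0.151, partial eta-squared = 0.13, d = 0.78.

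**The case against.** **The 80 % is not a slip of calculation.** It follows from a recognised power formula. This is true, and the fault is better described as a mismatch of effect-size scale than as bad arithmetic. But the sentence claims 80 % power for an effect of the cited size in the cited kind of test, and that claim is false however the number arose.

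**The route to 40 is inferred.** The article names no formula, software or correlation, and an article may leave such detail to the full protocol. This stands as a caution: the double counting is the likely explanation, not a documented one. The 29 % does not depend on it.

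**The cited trials are not at hand.** The recomputation assumes their values are ordinary partial eta-squared for the group × time term. That is how the Sample size section presents them, so the assumption follows the article's own wording, but it is an assumption.

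**The intention-to-treat analysis with last observation carried forward would include all 54.** Power would then be about 38 % (45 % at 0.06). This changes the degree, not the conclusion, and it supposes that carrying values forward leaves the effect undiminished.

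**The trial already calls itself a pilot and promises only an indication of efficacy.** That softens the consequence, and nothing in the article says a null result will be taken as proof of no effect. It does not correct a stated power that is wrong for the primary test. Leading with an interval estimate goes somewhat beyond correcting the error, but it is the natural reading of a trial of this size.

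**Conclusion.** The concern holds. For the effect size and test that the article names, power with 40 patients is about 29 %, not 80 %. Nothing that keeps 0.05 to 0.06 as a group × time partial eta-squared comes near the stated figure: the most favourable two-sided case, 0.06 with all 54 analysed, gives about 45 %. Power of 80 % for 0.05 would need about 152 evaluable patients, nearly four times 40. With 40, the trial has 80 % power only for a partial eta-squared of about 0.17, more than three times the planning value.

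This rests on one assumption, that the cited values are the usual partial eta-squared of the group × time test. It does not rest on any assumed pre-post correlation. Because the wrong figure concerns the primary endpoint and the error is large, it must be corrected.

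**What to change.** Keep the target of 54 and replace the power sentence in the Sample size section with, for example: *With 40 evaluable patients, power for a group × time partial eta-squared of 0.05 is about 29 % (two-tailed alpha 0.05); 80 % power is reached only for a value of about 0.17, that is, about 0.9 standard deviations of change.* Adding the figures for all 54 (38 %, and 80 % power at about 0.13) would cover the intention-to-treat analysis.

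In the Analyses section, say that the main result is the between-arm difference with its 95 % confidence interval, in keeping with the pilot status given under Aims, and that a non-significant p-value will not be read as lack of efficacy.

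The cost is wording only: no more patients, no new assessments and no change to the test. The stated power becomes less favourable.

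### The minimum of 53 patients (54 recruited) does not cover both stated losses: it keeps 40 for the EDE primary outcome, but about 37 for completer analyses of the computer tasks

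*Protocol article*

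**What the plan says.** All the figures stand in the Sample size section of the protocol article. The base is given as "a total sample size of 40 patients will have 80 % power to detect an effect of this size", for the group-by-time test in a 2 × 2 repeated measures ANOVA. Two losses follow. The first concerns the computer tasks: "The percentage of data lost owing to errors in the applied neuropsychological tasks was 7 % at the maximum in previous studies". The second is introduced with "Taking this and a potential dropout rate of 25 % into account", where the word this points back to the 7 %. The conclusion is that "a minimum of 53 patients must be included", and then: "Thus, we will recruit 27 patients for each group", 54 in total. No inflation formula is printed.

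Other sections show which outcomes each loss touches. The primary outcome is the change in objective binge-eating episodes on the EDE, an interview held at baseline and at the 2-month follow-up (Primary outcome measure; Table 1). Approach bias (Food-AAT) and attentional bias (visual probe task) are computer tasks done at baseline and post-treatment (Secondary outcome measures; Table 1). The Analyses section plans both completer and intent-to-treat analyses, the latter with last observation carried forward.

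**The concern.** The section presents 53 as the number that still leaves 40 after both losses. To keep 40 after a proportion is lost, one divides by the proportion retained. Division with both losses gives a figure in the high fifties, not 53. A reader would therefore take it that 40 patients with usable task data are expected, when the section's own inputs imply fewer.

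The outcomes at stake are approach and attentional bias. The protocol treats approach bias as the mechanism that the training targets, states directional hypotheses for both biases in the Aims, and plans regressions of symptom improvement on changes in the cognitive measures. The expected number for these analyses should be stated correctly, even though they are secondary.

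**Working it through.** **Inputs (all from Sample size).** Required evaluable number 40; task-data loss 7 % at most; dropout 25 %; stated minimum 53; planned recruitment 54, that is 27 per group.

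**Step 1: reproduce 53.** Several routes were tried, because the formula is not printed.

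| Route | Result | Rounded up |
|---|---|---|
| 40 × (1 + 0.25 + 0.07) | 52.8 | 53 |
| 40 × (1 + 0.3025), with 0.3025 = 1 − 0.75 × 0.93 | 52.1 | 53 |
| 40 × 1.25 × 1.07 | 53.5 | 54 |
| 40 × 1.25/0.93 | 53.8 | 54 |
| 40/0.75 (7 % left out) | 53.3 | 54 (53 if rounded down) |
| 40/(0.75 × 0.93) | 57.3 | 58 |
| 40/0.68 | 58.8 | 59 |

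The routes that use both losses and round up to 53 multiply by 1 plus the combined loss. Dividing by 0.75 alone gives 53 only if rounded down, and it omits the 7 %. So the multiplication is the likely source, but it is an inference.

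**Step 2: apply the losses to the recruited number.**

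| Recruited | Dropout only (× 0.75) | Both in sequence (× 0.75 × 0.93) | Both added (× 0.68) |
|---|---|---|---|
| 53 | 39.75 | 37.0 | 36.0 |
| 54 | 40.5 | 37.7 | 36.7 |
| 58 | 43.5 | 40.5 | 39.4 |
| 59 | 44.25 | 41.2 | 40.1 |

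With 54 recruited, the EDE keeps 40.5, while the tasks keep 37.7 or 36.7. The shortfall against 40 is 2.3 or 3.3 patients.

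**Step 3: number needed to keep 40 with task data.** In sequence it is 58, which splits evenly into 29 per group. If the losses add it is 59, or 60 under 1:1 allocation (30 per group).

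**Step 4: what the shortfall means for power.** The smallest cited partial eta squared is 0.05, so f² = 0.05/0.95 = 0.0526. For the group-by-time test take noncentrality λ = f² × N × 2/(1 − ρ), on 1 and N − 2 degrees of freedom, with two-sided α = 0.05. The pre-post correlation ρ is not given in the article and is assumed here. With ρ = 0.5 and N = 40, λ = 8.42 and power is 0.81, and 40 is the smallest even total that reaches 80 %. On the same model power is 0.76 at 36, 0.77 at 37 and 0.79 at 38. The base of 40 is sensitive to ρ: 56 would be needed at ρ = 0.3, and 26 at ρ = 0.7. The inflation arithmetic in Steps 1 to 3 does not depend on ρ.

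**The case against.** Four points on the other side have weight.

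- **The primary outcome is covered.** The EDE is an interview, so the 7 % does not apply to it, and 54 recruits keep 40.5. This stands in full. A stated minimum of 53 would give 39.75, but the trial recruits 54.
- **The timing of the 25 % is not stated.** The tasks end at post-treatment, the EDE two months later. If 25 % is the loss by follow-up, fewer will have left by post-treatment. With the 7 % applied, 54 recruits still leave 40 as long as dropout by post-treatment is about 20 % or less: 40/(54 × 0.93) = 0.797 must be retained. This stands as a limit on the size.
- **The 7 % is a ceiling, and it is worded as lost data rather than lost patients.** If errors remove only some trials of a task, fewer patients are lost. This also stands, although adding the 7 % to a patient count treats it as patients.
- **The intent-to-treat analysis carries the last observation forward and so keeps dropouts.** The shortfall therefore bears mainly on the completer analyses.

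These points reduce the shortfall, but they do not make 53 follow from inputs that the section says it has taken into account.

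A reader might draw two stronger conclusions. One is that the authors certainly multiplied where they should have divided. The article prints no formula, and leaving out the 7 % explains 53 too. The other is that the shortfall comes on top of a power error in the base of 40. This check shows no such error: 40 is reproduced at a correlation of 0.5. Whether 40 is well founded depends on the correlation and on how the published partial eta squared enters the calculation. The article states neither, and that is a separate question from the inflation.

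**Conclusion.** The sentence is wrong as written. Neither 53 nor 54 leaves 40 patients once both stated losses are taken off; 54 leaves 37.7 or 36.7, and keeping 40 takes 58, or 59 (60 with equal arms) if the losses add.

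The consequence is small. It is a shortfall of about 2 to 3 patients, and about 2 to 4 points of power if the correlation is 0.5, in completer analyses of approach and attentional bias. It assumes that the full 25 % has dropped out by post-treatment and that the 7 % maximum removes whole patients. The primary outcome and the recruitment target are unaffected, in a trial that describes itself as a pilot. The point is minor.

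**What to change.** Replace the sentence that gives the minimum of 53 with wording such as:

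*With 54 recruited and 25 % dropout we expect about 40 patients with EDE follow-up and, after up to a further 7 % task-data loss, about 37 with computer-task outcomes; 58 would be needed to retain 40 for the latter.*

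Quote the power at those two numbers, with the pre-post correlation that was assumed. It would also help to say at which timepoint the 25 % applies.

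The cost is wording only. Recruitment stays at 54, and the stated number for the task outcomes becomes slightly less favourable.
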